### Recruitment of participants and follow‑up

Data will be extracted from 1 January 2008 to 31 December 2019. The screening period will cover the 7 years from 1 January 2008 to 31 December 2014, which will allow us to identify patient eligibility criteria. All patients identified in the SNDS databases during the pre-selection period who met the inclusion criteria will be recruited in the study from 1 January 2015 to 31 December 2015. Participants will be followed for 4 years, until 31 December 2019 (Fig. 1).

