### Screening strategies and study allocation

Each patient will be assigned into one of the two study groups according to the CAD screening strategy performed during the recruitment period. Patients who had at least one CAD screening test will be assigned to the routine CAD screening group and included at the time of the first CAD test. Patients who did not perform any CAD screening (except for the resting electrocardiogram) will be assigned to the control group, and included at the time of the resting electrocardiogram, or at the time of a medical visit (general practitioner, diabetologist, or cardiologist), whichever comes first.

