### Outcomes

The primary outcome is the incremental cost per life-year gained over 4 years in CAD routine screening group versus no screening in the perspective of French health insurance. The key secondary health economic endpoints include the cost-consequence analysis linking the total 4-year direct costs of each strategy and clinical endpoints; an analysis of budget impact for the French Insurance system to promote the routine CAD screening; and the total care consumption during follow-up. The key secondary clinical endpoints included the effects of CAD screening (versus no screening) in terms of major adverse cardiovascular events (a composite of acute coronary syndrome, coronary revascularization, or hospitalization for heart failure); all-cause mortality; major cerebrovascular events (a composite of stroke, hospitalization for TIA, or carotid revascularization); major adverse limb events (a composite of ischemic diabetic foot, lower-limb revascularization or amputation); and CKD or end-stage kidney disease (ESKD, requirement of any sustained haemodialysis or kidney transplantation). Each component of these composite endpoints will also be considered individually. Major cerebrovascular events, major adverse limb events and ESKD will be assessed during follow-up among participants without a baseline history of each condition (as appropriate). Finally, SCADIAB will also assess the frequency of routine CAD screening, expressed as the number of examinations performed yearly per individual.

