### Causal effects of interest

The primary causal effect in our study is the intention-to-treat effect. That is the comparative effect of being assigned to the CAD screening strategies at inclusion, regardless of whether the individuals continue following the strategies during follow-up. The per-protocol effect will also be investigated after exclusion of participants from the control group who underwent routine CAD screening during follow-up.

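### Controls are selected on having no CAD test in 2015 but are followed from an earlier visit, so allocation uses information from after time zero and, taken alone, favours screening on mortality and life-years

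*Protocol article*

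**What the plan says.** Under Screening strategies and study allocation, the protocol article sets the arm by what happens over a window: "Each patient will be assigned into one of the two study groups according to the CAD screening strategy performed during the recruitment period". Under Recruitment of participants and follow-up, that window is the calendar year in which patients "will be recruited in the study from 1 January 2015 to 31 December 2015".

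Time zero differs by arm. A patient with at least one test is "assigned to the routine CAD screening group and included at the time of the first CAD test". For the other arm, "Patients who did not perform any CAD screening (except for the resting electrocardiogram) will be assigned to the control group", and they are "included at the time of the resting electrocardiogram, or at the time of a medical visit (general practitioner, diabetologist, or cardiologist), whichever comes first".

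The section Causal effects of interest defines the primary effect as intention-to-treat: "the comparative effect of being assigned to the CAD screening strategies at inclusion". Excluding controls who are screened during follow-up is reserved there for the per-protocol effect.

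The Outcomes section makes life-years the denominator of the main result: "The primary outcome is the incremental cost per life-year gained over 4 years in CAD routine screening group versus no screening". The only adjustment described under Statistical analysis is a high-dimensional propensity score with inverse probability weighting on baseline characteristics.

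**The concern.** Two patients show the problem. The first is seen by a general practitioner in January 2015 and has a CAD test in September. She joins the screening arm in September, and her eight event-free months count in neither arm. The second is seen in January and dies in March without a test. He is a control with an early death. On the visit date nothing distinguished them. What happened afterwards decided their arms.

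Deaths in 2015 before any test thus all fall to the controls, while part of the untested, event-free time that should go with them is discarded. The control death rate is raised even if screening does nothing.

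This conflicts with the stated estimand. A patient who would be a control on the visit date but is tested later in 2015 is taken out of the control arm before the intention-to-treat analysis starts. The article otherwise allows that kind of exclusion only in the per-protocol analysis. Baseline weighting does not help, because the fault lies in how person-time is allocated and not in covariate imbalance.

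At stake are all-cause mortality and the primary cost per life-year gained. If the true difference in life-years is small, a spurious gain of days or weeks can dominate the ratio.

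**Working it through.** The article states no sample size, event rate or share tested, so it has no figure to reproduce. The check applies the allocation rule as written when screening has no effect.

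**From the article:** a 12-month allocation window (1 January to 31 December 2015); screened time zero at the test; control time zero at the first ECG or visit; a 4-year horizon.

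**Assumed, not in the article:** constant death hazard λ per year; share p tested within 2015 at a constant rate θ = −ln(1−p); testing unrelated to prognosis.

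**Closed form, with control time zero at 1 January.** Let s = λ + θ. As fractions of all patients:

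- controls who die in 2015 untested: a = (λ/s)(1 − e^−s)
- controls alive and untested at the end of 2015: b = e^−s
- control 4-year risk: [a + b(1 − e^−3λ)] / (a + b)
- screened 4-year risk: 1 − e^−4λ

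With λ = 0.05 and p = 0.30: θ = 0.3567, s = 0.4067, b = 0.6659 and a = 0.0411.

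- Control 4-year risk: (0.0411 + 0.6659 × 0.1393) / 0.7069 = 18.9%
- Screened 4-year risk: 1 − e^−0.20 = 18.1%, so the ratio is 0.96
- First-year risk: controls 0.0411 / 0.7069 = 5.8%; screened 1 − e^−0.05 = 4.9%; ratio 0.84

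Life-years over 4 years in the same case:

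- screened: (1 − e^−0.20)/0.05 = 3.625
- controls: {λ[(1 − e^−s)/s² − e^−s/s] + b[1 + (1 − e^−3λ)/λ]} / (a + b) = (0.0192 + 2.5208) / 0.7069 = 3.593
- spurious gain: 0.032 life-years, about 12 days

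**Simulation, with a control's first visit exponential with mean 1 month** (3 million patients per scenario, λ = 0.05). The risk columns are from the closed form.

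| Tested in 2015 | 4-year risk, control | 4-year risk, screened | Risk ratio | Simulated 4-year rate ratio | Simulated year-1 rate ratio | Spurious life-years |
|---|---|---|---|---|---|---|
| 10% | 18.4% | 18.1% | 0.99 | 0.98 | 0.97 | 0.008 |
| 20% | 18.6% | 18.1% | 0.97 | 0.97 | 0.91 | 0.017 |
| 30% | 18.9% | 18.1% | 0.96 | 0.96 | 0.86 | 0.027 |
| 50% | 19.9% | 18.1% | 0.91 | 0.91 | 0.73 | 0.061 |

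The later visit lowers the gain at 30% tested from 0.032 to 0.027 life-years (about 10 days). The simulation carries error of about 1% in the ratios, so small differences between low testing shares should not be read.

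**Wider range.** Over 3-7% annual mortality, the 4-year rate ratio is about 0.98-1.00 with 5-10% tested, 0.95-0.98 with 15-30% and 0.91 with 50%. The spurious gain runs from about 0.001 to 0.08 life-years.

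**Scale.** At λ = 0.05, a true 5% cut in mortality gives 3.643 − 3.625 = 0.018 life-years over 4 years. A 10% cut gives 0.035 and a 20% cut 0.071.

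**Aligned time zero, same null.** Censoring untested time at a 2015 test gives rate ratios of 0.99-1.01. Starting both arms on 31 December 2015 also gives 0.99-1.01. The bias comes from the allocation rule and disappears when the rule is aligned.

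**The case against.** **The reading is partly inferred.** The article does not say in so many words that controls must be test-free through all of 2015; this follows from the recruitment dates and the allocation rule together. The statement "Participants will be followed for 4 years, until 31 December 2019" is exact only for a start at the end of 2015, and the design figure is not shown. If controls had to be alive on 31 December 2015, the bias would reverse, to a rate ratio of about 1.31. But no such requirement is stated, and the allocation section ties inclusion to a visit or test date. If a control were fixed at the visit, a patient seen in January and tested in September would belong to both arms, whereas the article places every patient tested in 2015 in the screening arm. The ambiguity itself needs resolving.

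**The size is assumed.** This stands. With few patients tested the bias is 1-2% or less, and how large it looks depends on the benchmark chosen.

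**Details may sit elsewhere.** The article refers to an earlier published protocol and an approved amendment. However, its stated purpose is to report the target trial emulation, and the allocation rule it prints is specific.

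**Stronger readings that the article does not support.**

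- A reader might infer that major cardiovascular events are also biased towards screening. The calculation covers death only. A work-up after a coronary event could itself count as a CAD test and move the patient to the screening arm, so the direction is uncertain.
- A reader might infer a cost bias because a visit before the test falls outside screened follow-up. The article does not say that a visit led to the test, and no amount can be derived.
- A reader might infer that the final estimate must favour screening. Confounding by indication may act the other way. With 20% of patients at three times the hazard and tested twice as often, the unadjusted rate ratio is 1.13. It is 1.21 with a common landmark, so the time-zero error is still present, merely offset.

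**Conclusion.** The point holds for all-cause mortality and life-years gained. As written, the arm depends on testing after a control's time zero. That contradicts assignment at inclusion, and the planned baseline weighting cannot remove it. The direction of this component, taken alone, is towards screening, provided controls are not required to survive 2015.

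Its size rests on a constant death hazard, testing at a constant rate unrelated to prognosis, and an early first visit. It ranges from negligible when few patients are tested to about a 9% lower 4-year mortality rate when half are tested. In the middle of that range (5% annual mortality, 30% tested), the spurious gain of 0.027 life-years exceeds what a true 5% cut in mortality would give. No conclusion is drawn on non-fatal coronary events, on costs, or on the net direction after confounding. The defect lies in the primary comparison and can be corrected in the analysis, so it should be corrected before the analysis is run.

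**What to change.** Rewrite the allocation rule so that eligibility, assignment and time zero fall on the same date in both arms. Two routes are suitable:

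1. Sequential nested trials through 2015. At each start date, eligible and not-yet-tested patients are assigned on what is known then. Controls tested later stay in the control arm for intention-to-treat.
2. A common qualifying visit or ECG as time zero, with a short grace period and clone-censor-weight. Clones assigned to no screening are censored when tested within the grace period, and weighted for that censoring.

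In either case, bootstrap the variance by person, because one patient can contribute more than once.

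At minimum, add a landmark analysis starting both arms on 31 December 2015. It removes the bias under the null and fits four years to 31 December 2019. It restricts inference to patients who survive 2015, and the cost of the 2015 test falls before the landmark, so alone it cannot carry the cost per life-year.

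The article should also say whether controls must be test-free for all of 2015 and whether they must be alive at its end.

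The cost is wording and more programming on claims data, with no new recruitment. Controls tested later in 2015 will dilute the intention-to-treat contrast somewhat.

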### Eligibility criteria

The key inclusion criteria are patients aged 40 years or older, with T2DM for at least 7 years, two or more additional cardiovascular risk factors (obesity, hypertension, hypercholesterolemia, or tobacco smoking), and at least one microvascular or macrovascular disease: carotid stenosis, transient ischemic attack (TIA), stroke, lower-limb peripheral artery disease, chronic kidney disease (CKD), severe diabetic retinopathy requiring laser photocoagulation, or peripheral or autonomic diabetic neuropathy. The main exclusion criteria include the presence of CAD (a history of acute coronary syndrome, coronary revascularization, angina pectoris, or unstable angina), the performance of one or more CAD screening tests, or any visit to an emergency department for chest pain resulting for admission to a cardiac intensive care unit.

### Outcomes

The primary outcome is the incremental cost per life-year gained over 4 years in CAD routine screening group versus no screening in the perspective of French health insurance. The key secondary health economic endpoints include the cost-consequence analysis linking the total 4-year direct costs of each strategy and clinical endpoints; an analysis of budget impact for the French Insurance system to promote the routine CAD screening; and the total care consumption during follow-up. The key secondary clinical endpoints included the effects of CAD screening (versus no screening) in terms of major adverse cardiovascular events (a composite of acute coronary syndrome, coronary revascularization, or hospitalization for heart failure); all-cause mortality; major cerebrovascular events (a composite of stroke, hospitalization for TIA, or carotid revascularization); major adverse limb events (a composite of ischemic diabetic foot, lower-limb revascularization or amputation); and CKD or end-stage kidney disease (ESKD, requirement of any sustained haemodialysis or kidney transplantation). Each component of these composite endpoints will also be considered individually. Major cerebrovascular events, major adverse limb events and ESKD will be assessed during follow-up among participants without a baseline history of each condition (as appropriate). Finally, SCADIAB will also assess the frequency of routine CAD screening, expressed as the number of examinations performed yearly per individual.

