## Background

Type 2 diabetes mellitus (T2DM) is a substantial health problem with a high clinical and economic burden [1, 2]. Despite a recent prognostic improvement, coronary artery disease (CAD) remains one of the leading causes of mortality in people with T2DM [3]. CAD is often severe and silent in patients with T2DM [4], prompting screening in asymptomatic individuals. Previous randomised controlled trials (RCTs) have failed to provide evidence of the effectiveness of routine CAD screening in reducing major cardiovascular events and mortality in people with T2DM at moderate to high cardiovascular risk [5–9]. However, doubts remain about T2DM patients at a very high cardiovascular risk, who can benefit from this screening strategy, but in whom trials have not yet been conducted. Despite this lack of concrete evidence, current clinical practice and guidelines recommend routine CAD screening for silent CAD in individuals with diabetes at high cardiovascular risk [10]. The widespread practice CAD screening results in significant healthcare costs due to invasive testing, revascularisation procedures, and intensified pharmacological therapies. The cost-effectiveness of routine CAD screening has not been prospectively evaluated in T2DM people. Only two economic studies based on Markov models have addressed this issue by comparing screening versus no screening strategy in Japanese and American populations [11, 12]. The results of these studies were inherently limited by assumptions inherent in the models, uncertainties in the epidemiological and cost data, and variations in health care costs between countries.

In the midst of this discrepancy between the lack of tangible evidence and clinical practice, we are conducting the Cost-effectiveness of Screening of Coronary Artery disease in patients with type 2 DIABetes at a very high cardiovascular risk (SCADIAB) study to estimate the cost-effectiveness of routine CAD screening in T2DM patients with a very high cardiovascular risk.

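### The primary ratio is labelled as screening versus no screening over 4 years, but its control arm is no CAD screening test in 2015 followed by usual care, which can include later screening

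*Protocol article*

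**What the plan says.** The Outcomes section defines the primary endpoint: "The primary outcome is the incremental cost per life-year gained over 4 years in CAD routine screening group versus no screening". Under Screening strategies and study allocation, patients are placed in groups "according to the CAD screening strategy performed during the recruitment period", and the control rule is: "Patients who did not perform any CAD screening (except for the resting electrocardiogram) will be assigned to the control group". The Recruitment section fixes that period: eligible patients "will be recruited in the study from 1 January 2015 to 31 December 2015", with follow-up to the end of 2019.

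Causal effects of interest makes intention-to-treat primary, "regardless of whether the individuals continue following the strategies during follow-up". It adds a per-protocol effect from which controls who had routine screening during follow-up are excluded.

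Three other statements bear on the point. The Background says that "current clinical practice and guidelines recommend routine CAD screening for silent CAD in individuals with diabetes at high cardiovascular risk" and calls the practice widespread. The Eligibility criteria exclude patients for "the performance of one or more CAD screening tests"; no window stands beside that criterion, but the Recruitment section says of the eligibility look-back: "The screening period will cover the 7 years from 1 January 2008 to 31 December 2014". The Outcomes section also plans to report how many examinations each person has per year.

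**The concern.** The named comparator is 4 years without screening. The comparator that the assignment rule and the intention-to-treat effect produce is one year's classification followed by whatever testing usual care brings. The article itself foresees controls being screened later, and its Background makes this plausible.

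For a single clinical effect, such crossover is usually read as dilution towards no difference. A cost-effectiveness ratio need not behave that way, because numerator and denominator can be diluted by different amounts. A control tested in year 3 may bring most of the cost of a test and any procedure into the control arm, while little of the 4-year window remains in which to gain life-years. If so, incremental cost shrinks more than incremental life-years, and screening looks cheaper per life-year than it would against a truly unscreened group. For a health-insurance decision that is the unsafe direction.

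**Working it through.** **No figure to reproduce.** The article gives no cost, mortality, effect size or late-testing rate. What follows is illustrative; only the 4-year horizon and the 2015 window come from the document.

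**General condition.** Let p be the share of controls screened late, h the share of the cost of immediate screening that a late test incurs by year 4, and g the share of the immediate life-year gain that it achieves by year 4. Then

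intention-to-treat ratio / ratio versus no screening = (1 − p·h) / (1 − p·g).

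With positive cost and life-year differences, this is below 1 exactly when h > g.

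**Model by testing rate.** T = 4 years; controls can be tested from w = 1 year after entry at a constant rate r. A constant hazard reduction after the test makes the life-year gain proportional to the square of the time left. Writing f(s) = r·exp(−r(s−w)) and integrating over s from w to T:

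- share of controls tested: c = 1 − exp(−r(T−w))
- A = ∫ f(s)·(T−s)/T ds (control cost if it accrues evenly over the time left)
- B = ∫ f(s)·((T−s)/T)² ds (control life-year gain)

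The ratio is (1−c)/(1−B) if all cost falls at the test, (1−A)/(1−B) if all cost accrues, and (1−c/2−A/2)/(1−B) if half does each. For r = 10%: c = 1 − exp(−0.3) = 0.2592, so 0.7408/0.9477 = 0.78 with all cost at the test, and 0.8980/0.9477 = 0.95 with all cost accruing.

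| r per year | c | A | B | All cost at test | Half | All accruing |
|---|---|---|---|---|---|---|
| 3% | 0.0861 | 0.0328 | 0.0165 | 0.93 | 0.96 | 0.98 |
| 5% | 0.1393 | 0.0535 | 0.0271 | 0.88 | 0.93 | 0.97 |
| 10% | 0.2592 | 0.1020 | 0.0523 | 0.78 | 0.86 | 0.95 |
| 20% | 0.4512 | 0.1860 | 0.0975 | 0.61 | 0.76 | 0.90 |

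An understatement of 5% is reached at about 2% per year if all cost falls at the test, and at about 10% per year if all cost accrues. With w = 0.5, the all-at-test values are 0.92, 0.88, 0.77 and 0.59.

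**Survival check.** Exponential survival with assumed mortality of 3% or 5% a year, hazard ratio 0.8 or 0.9, late tests spread evenly over years 1 to 4 and all cost at the test gives 0.92–0.93 for p = 10%, 0.76–0.78 for p = 30% and 0.59–0.61 for p = 50%.

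**Where the direction fails.** With tests spread evenly over years 1 to 4, g = mean of ((4−t)/4)² = 0.1875, and h runs from 0.375 (all accruing) to 1 (all at the test).

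- If cost and benefit both accrue linearly, h = g and the ratio is 1.00.
- If late-tested controls gain three times as much per test and costs accrue, g = 3 × 0.1875 = 0.5625 > 0.375. For p = 10% to 50% the ratio is 1.02 to 1.13, so screening looks too dear.
- With all cost at the test, reversal needs a gain above 1/0.1875 = 5.3 times; sixfold gives 1.01 to 1.14.
- If the life-year difference is zero or negative, the ratio has no usable direction.

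**Per-protocol rule.** A control can be excluded for late screening only after surviving to the test. Controls who die early cannot be excluded in this way, while some who live longer are. Exclusion therefore selects on survival, and also on whatever risk prompted the later test. Dropping these people altogether also discards their unscreened time.

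**The case against.** The strongest defence is that nothing is hidden. Intention-to-treat is declared, its definition says that later departures are ignored, a per-protocol effect is planned without being limited to clinical endpoints, and yearly test counts will show how much late testing occurs. The article also condenses a design paper published earlier, so detail on weighting may lie elsewhere. Much of this stands: intention-to-treat is a legitimate primary effect for a strategy begun at entry, and the fault lies in the label and its interpretation. It does not cover the primary outcome's stated comparator, which the article's own rules do not deliver, or an exclusion rule that the article states outright and that conditions on the future.

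Three stronger readings are tempting and not supported.

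- A reader might infer that late tests definitely remove more cost than life-years. That needs front-loaded cost, similar benefit per test and a positive life-year gain, none of which is given. The Background lists intensified drug therapy among the costs, which accrues over time, and reports that earlier trials in lower-risk patients showed no mortality benefit.
- A reader might infer that controls are known to be untested in 2015 only. The prior-test exclusion makes it probable that they were also untested in the look-back years. That does not restrict testing in 2016–2019.
- A reader might carry the bias into the 5-year budget impact. The article does not say where that analysis takes its costs, and an analysis of spreading screening may well be set against current practice, which includes some screening.

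**Conclusion.** The mismatch is certain from the text: the primary ratio is not a comparison with 4 years of no screening, and the planned per-protocol analysis does not turn it into one. Bias in favour of screening is the likelier direction, since testing and procedures are paid for near the test while life-years accrue over the time left, but it is not established. The size cannot be derived from the documents. Under the assumptions shown, with control testing at 3% to 20% per year, the ratio is understated by about 2% to 10% if costs accrue and 7% to 39% if all cost falls at the test, the latter being the extreme for cost timing. This is a worthwhile and inexpensive correction; it is not a reason to abandon the intention-to-treat analysis.

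**What to change.** 1. In Outcomes and Causal effects of interest, keep the intention-to-treat ratio and name its comparator as *no CAD screening test in the 2015 recruitment period, usual care thereafter*. Report the cumulative share of controls screened by year.
2. Replace the per-protocol exclusion with censoring of controls at their first routine CAD screening test after inclusion, weighting both costs and survival by the inverse probability of remaining unscreened, in addition to the planned baseline weights.
3. Censor at routine tests, not at any CAD test. Symptom-driven testing also happens under a no-screening strategy, so its costs belong in that arm. Censoring at every test would remove them and would estimate a never-tested comparator instead.
4. Rest any statement of cost per life-year versus no screening on that analysis.

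The cost is some wording and one weighted analysis, using the claims data that the study already plans to extract. The downsides are wider intervals, reliance on measured predictors of later screening, and the need to separate routine from symptom-driven tests in claims data. That separation needs a stated rule and a sensitivity analysis.

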### Statistical analysis

The gross estimate of the incremental cost per life-year gained at 4 years will be conducted. High dimension propensity score will be used to balance the baseline characteristics of participants. Comparisons between study groups will be performed without adjustment; and with adjustment for confounding factors using the weighted by inverse probability of receiving treatment (IPTW). A cost-consequence analysis will be performed linking results of all direct costs, and results on major cardiovascular events. A budget impact analysis will be conducted to determine the public expenses of the spread of a routine CAD screening at 5 years from French health insurance perspective. The risk of clinical outcomes by study groups will be assessed using IPTW proportional hazards survival regression models. We will also consider the competing risk of all-cause death.

We will perform subgroup analyses by sex, age and frequency of CAD tests. Finally, a sensitivity analysis is planned to assess the interest of routine CAD screening in T2DM people with at least 2 cardiovascular risk factors without microvascular or macrovascular disease.

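### The key secondary MACE composite counts every coronary revascularisation, including those the screening test prompts, so it cannot be read as clinical benefit or harm

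*Protocol article*

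**What the plan says.** All references are to the Protocol article.

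- **Outcomes:** the first key secondary clinical endpoint is "major adverse cardiovascular events (a composite of acute coronary syndrome, coronary revascularization, or hospitalization for heart failure". No qualifier separates urgent from elective procedures, and no interval after the screening test is set aside. The same section says that the components of each composite will also be looked at one by one. It makes cost per life-year gained over 4 years the primary outcome.
- **Background:** widespread screening "results in significant healthcare costs due to invasive testing, revascularisation procedures, and intensified pharmacological therapies".
- **Screening strategies and study allocation:** patients with a test are "assigned to the routine CAD screening group and included at the time of the first CAD test". Controls enter at a resting electrocardiogram or a medical visit.
- **Eligibility criteria:** the exclusions include "the presence of CAD (a history of acute coronary syndrome, coronary revascularization, angina pectoris, or unstable angina", so any revascularisation counted is a new one.
- **Causal effects of interest:** "The primary causal effect in our study is the intention-to-treat effect".
- **Statistical analysis:** "The risk of clinical outcomes by study groups will be assessed using IPTW proportional hazards survival regression models". The cost-consequence analysis is described as "linking results of all direct costs, and results on major cardiovascular events".

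**The concern.** In this study revascularisation plays two roles. It is an intended downstream step of the strategy under evaluation, because a positive test in a patient without symptoms can lead to it. It is also scored as an adverse event of the same standing as an acute coronary syndrome (ACS) or a heart-failure admission. Since time zero in the screened group is the test itself, procedures that the test prompts fall inside follow-up. Controls have no matching trigger at their own time zero.

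The composite therefore mixes two quantities that screening may move in opposite directions: acute events, which it is meant to reduce, and procedures, which it is expected to increase. A ratio near or above 1 could mean no clinical benefit, or it could mean benefit masked by procedures. Inverse-probability weighting does not help, because it balances baseline characteristics and these events arise after allocation. The study is meant to inform resource allocation and clinical decisions, so an ambiguous clinical result beside the costs matters.

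**Working it through.** The article states no event rate, screening yield, effect size or power calculation, so there is no figure of its own to reproduce. Every rate below is an assumption, used to show how many test-prompted procedures are enough to matter.

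**First calculation: 4-year risks**

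Inputs (all assumed):
- p = control risk of ACS or heart-failure hospitalisation, 12% (range 8% to 16%)
- r = other revascularisation, 2% in both groups
- t = extra revascularisation in the screened group prompted by the test, net of any such procedures in controls
- true effect on ACS/heart failure: none, or a 15% reduction

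Revascularisation is taken as independent of ACS/heart failure.

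Control composite = 1 − (1 − p)(1 − r) = 1 − 0.88 × 0.98 = 13.76%.

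Screened composite with no true effect = 1 − 0.88 × (0.98 − t):
- t = 2%: 15.52%, ratio 1.13
- t = 4%: 17.28%, ratio 1.26
- t = 6%: 19.04%, ratio 1.38

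Screened composite with a 15% reduction (ACS/heart failure 0.85 × 12% = 10.2%) and t = 4%: 1 − 0.898 × 0.94 = 15.59%, ratio 1.13.

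The two groups show equal composite risk when t = 1 − r − (1 − p)(1 − r)/(1 − 0.85p):

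| p | Control composite | ACS/heart failure after 15% reduction | Break-even t |
|---|---|---|---|
| 8% | 9.84% | 6.8% | 1.26% |
| 12% | 13.76% | 10.2% | 1.96% |
| 16% | 17.68% | 13.6% | 2.72% |

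*Displacement of later procedures.* If early procedures replaced half of the other 2% in the screened group (r = 1% there), break-even at p = 12% becomes 0.99 − 0.8624/0.898 = 2.96%. If they replaced all of it, 1.00 − 0.8624/0.898 = 3.96%.

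**Second calculation: cumulative hazards, benefit on ACS only**

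With H = −ln(1 − risk), composite ratio = [HR × H(ACS) + H(HF) + H(rev) + H(extra)] / [H(ACS) + H(HF) + H(rev)].

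Assumed control risks are ACS 6%, heart failure 8% and revascularisation 4%, with a true ACS hazard ratio of 0.80. The hazards are 0.0619, 0.0834 and 0.0408, total 0.1861.
- Three extra points, H(extra) = 0.0305: (0.0495 + 0.0834 + 0.0408 + 0.0305)/0.1861 = 1.10
- One, two and five extra points: 0.99, 1.04 and 1.21
- Break-even: 1 − exp(−0.20 × 0.0619) = 1.2 points
- ACS plus heart failure only: 0.915

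Over nine scenarios (ACS 4% to 8%, heart failure 5% to 12%, revascularisation 3% to 6%, ACS hazard ratio 0.7 to 0.9), break-even runs from 0.4 to 2.5 points. The composite ratio is 0.95 to 1.05 at one extra point, 0.98 to 1.13 at two, and 1.02 to 1.22 at three. The ACS plus heart-failure ratio is 0.87 to 0.96 throughout.

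**The case against.** Much of the case on the other side stands.

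- *The primary outcome is untouched.* It rests on costs and survival, and all-cause mortality is a separate key secondary endpoint. This stands and limits the severity.
- *Components will be reported individually.* A pattern of more procedures and fewer acute events would be visible. This stands as partial mitigation. It leaves unchanged both the composite and its place beside the costs.
- *This is not estimation bias.* A reader might infer that the comparison is biased by construction. The documents do not support that. The target is the intention-to-treat effect of the strategy, and if screening causes more procedures, that is a true effect on the endpoint as defined. The fault is in what the endpoint measures.
- *Nothing is charged twice.* A reader might infer that a procedure is deducted both as cost and as consequence. No formula or ratio is given in which that would happen. The Outcomes section speaks of clinical endpoints in general, although Statistical analysis names only major cardiovascular events.
- *A qualifier may exist elsewhere.* The article is an update of a design published earlier and not shown here. An urgency rule there is possible, but the definition printed in this article carries none.
- *The figures are assumptions.* Displacement of later procedures, or overlap between procedures and acute events, would raise the break-even, as the displacement figures show. Controls screened during follow-up would lower the net excess in the intention-to-treat analysis. The per-protocol analysis removes those controls and could widen it.

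**Conclusion.** The point holds as a weakness in a key secondary endpoint that should be fixed. As printed, the composite counts procedures that the strategy itself prompts, so it cannot be read as clinical benefit or harm, and the cost-consequence analysis linked to it inherits that ambiguity.

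A net 1.3 to 2.7 percentage points of test-prompted procedures would hide a 15% reduction in ACS/heart failure, given a control risk of 8% to 16%, 2% other revascularisation in both groups, independence and no displacement. Nothing in the article says whether the actual excess is above or below this.

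A reader might infer that screening will appear harmful. That goes too far: reversal is possible, not certain, and with one or two extra points the hazard calculation gives ratios on both sides of 1. The upward push on the composite follows from the definition and the time zero; its size does not.

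**What to change.** 1. Make ACS plus hospitalisation for heart failure the composite for the clinical comparison and for the cost-consequence analysis. Optionally add revascularisation performed during an ACS or unplanned stay.
2. Keep the present composite as a secondary analysis.
3. Report other revascularisation by group as a process and cost outcome of the strategy.

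**Cost.** The minimal version needs no new data, because the components are already to be analysed separately; it takes protocol and SAP wording and one more derived variable. The optional version needs a claims rule based on discharge diagnosis and mode of admission, with some misclassification of urgent and elective procedures. Either way there are fewer events. Elective procedures for newly symptomatic disease, which are real outcomes of not screening, also leave the main composite, though they stay visible in the component analysis. Analysis was due to start before the end of 2023, so any change made after it began should be labelled post hoc.
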